## 7.12 Definition of End of Trial

The end of the study is defined as the last participant’s last data capture.

# 8. STUDY INTERVENTION

## 8.1 Intervention Group (intervention description)

The Oto Tinnitus Programme is a digital therapeutic combining CBT with mindfulness, patient education and physical therapy (physical stretches/exercises). Oto’s programme offers a series of daily therapy sessions, where the user listens to recorded audio content that takes them through education, cognitive exercise or a tinnitus-specific meditation, and optional 1-1 chat support. Users work their way through progressive modules using a spiral curriculum, where the sessions build on techniques and exercises learned in previous sessions. The programme lasts approximately 6 weeks, using the app 4-5 times per week, which evidence suggests is sufficient time for a therapeutic difference. Users can personalise their therapy by listening to additional modules and sounds from the sound library.

Participants are expected to have completed the intervention in approximately six weeks.

## 8.2 Control Group

Those allocated to the control arm of the study will undertake one to one tinnitus tinnitus therapy from a trained Audiologist/Hearing Therapist/Psychologist via video calls. This is not a direct mirror of NHS practice as patients will have rapid access to therapy, rather than typical long waiting times from GP referral. Participants in the control group will agree to not use Oto or an alternative tinnitus app for the duration of the study.

This control intervention will consist of a minimum of 1 tinnitus therapy session, with further sessions at the discretion of the participant and therapist up to a maximum of 6. Therapy will begin within 1 week of randomisation. There will be a panel of therapists selected to deliver the therapy. The therapy will include several elements of current standard care formulated into a personal management plan. :

- Assessment of participant needs
- Participant education
- CBT
- Relaxation therapy
- Signposting to hearing aid fitting and other support

In order to facilitate retention, participants in the control group will be offered the Oto Tinnitus Programme at the end of the 12-month RCT period.

Therapists will provide data to Lindus Health on attendance and number of sessions for each participant.

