### 7.10.3 Month 6 (Study week 26 +/- 14 days)

To collect data to include but not limited to:

- Complete TFI questionnaire
- Complete EQ-5D-5L and HUI3 questionnaires
- Complete questionnaire on primary and community healthcare appointments and A&E visits related to tinnitus since week 12
- Complete questionnaire on personal out-of-pocket tinnitus related costs, any time-off work and travel information to appointments incurred since week 12
- Any change in medication (particularly medications known to be associated with tinnitus, e.g. Aspirin, diuretics) or introduction of hearing aid

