## 8.3 Concomitant Therapy

Participants will be directed to contact their GP for hearing aid referral to a rapid access service such as is provided by accredited ‘Any Qualified Provider’ (AQP) high street audiologists. Any form of hearing aid provision including tinnitus maskers will be permitted and this will be recorded via participant questionnaire.

No medication is administered within the study, nor are any medications prohibited.

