## 10.1 Description of Statistical Methods

The primary analysis will be conducted on the intention-to-treat (ITT) population. In addition to this, a per-protocol analysis will also be planned as a sensitivity analysis. Compliance will be defined as a minimum of 60 minutes of total use for the intervention group, and one or more sessions for the CBT group. Participants reporting poor compliance will be recorded and these participants will be included in the ITT analysis. Adherence to the smartphone app delivered programme will be monitored through the app with results analysed by intention-to-treat (ITT).

The primary outcome will be reduction in total TFI score at the 6 month point in the ITT population. Non-inferiority will be assessed by constructing a 95% confidence interval around the mean difference in TFI reduction between the groups, and comparing the -upper bound of the confidence interval to the pre-specified non-inferiority margin.

A secondary analysis of the primary outcome will examine significant differences between the control and intervention group’s TFI score at 6 months using a general linear model or a comparable suitable method, using the stratification variables and other potential confounding variables as covariates.

As a sensitivity analysis, the primary outcome will be analysed using the Per-Protocol (PP) population, which consists of participants complying with the treatment regimen. Compliance will be defined as a minimum of 60 minutes of total use for the intervention group, and one or more sessions of CBT for the control group.

Secondary outcomes will be compared between groups and over time with mixed-effects regression models for repeated measures, using the stratification variables and other potential confounding variables as covariates. Logistic models will be used for binary outcomes, and Gaussian models for continuous outcomes. An interim analysis may be conducted once a sufficient number of participants have completed the 6 month milestone. The results of the interim analysis do not influence the continuation of the trial.

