# 24. APPENDIX 3 – CONTROL ARM INTERVENTION SPECIFICATION

Control arm intervention – specification

The standard care intervention was developed based on relevant guidance (BSA Practice Guidance Tinnitus in adults 2021 and NICE guidelines (NG-155)) and via consultation with clinicians providing NHS tinnitus therapy.

New assessment (approximately 60 minutes) to include:

1. Information gathering and education

- Detailed audiological history to include onset, progression, nature and impact of tinnitus at home/work/social, on sleep, mental health and quality of life.
- Explanation of tinnitus, tailored to the patients’ needs and understanding, usually based on a neurophysiological model (Jastreboff PJ, 1990) or cognitive behavioural model (McKenna et al 2014)
- Explanation of how hearing loss may influence tinnitus awareness
- Discussion of options for treatment/ rehabilitation

Questionnaires should be administered as appropriate to assess tinnitus handicap, anxiety and depression in order to establish the functional impact of tinnitus and guide appropriate management, and if appropriate onward referral to other specialties. Example questionnaires for this purpose include: Tinnitus Handicap Inventory; Tinnitus Functional Index; Hospital Anxiety and Depression Scale; Insomnia Severity Index

2. Individual Management Plan

These should be formulated individually, agreed with the participant and may include:

- Relaxation Therapy: Exercises, apps, refer to physio where indicated/available
- CBT: where available. Clinicians may undertake CBT if they have appropriate training and experience to do so. Others may suggest CBT exercises as part of therapy where appropriate, or signpost to other local services, where these exist.
- Signposting for equipment to facilitate sound enrichment and relaxation
  - - Sound generators with/ without pillow speakers
    - Ear level or in the ear sound generators
    - Relaxation CD
- Recommendation for hearing aid fitting where hearing loss is present and discussion of combination hearing aid/ tinnitus maskers where relevant
- Information leaflets which include websites with more information about tinnitus and products available
- Tinnitus UK
- Royal National Institute for the Deaf
- Treatment for anxiety/depression: signpost to local wellbeing service or to GP for antidepressant medication

Follow-up appointments if indicated (30 min routine/ 45 min complex) to include:

- Revision of history of changes

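### The per-protocol set keeps participants who also received the other arm's treatment, and outside therapy is not addressed for the Oto arm, so agreement between ITT and per-protocol does not check for this bias

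*Protocol*

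**What the plan says.** Section 8.2 places a limit on the control arm: "Participants in the control group will agree to not use Oto or an alternative tinnitus app for the duration of the study". Section 8.1, which describes the Oto programme, has no counterpart. Section 8.3 covers hearing aids and medication for everyone: "Any form of hearing aid provision including tinnitus maskers will be permitted and this will be recorded via participant questionnaire", and "No medication is administered within the study, nor are any medications prohibited". It is silent on therapist-delivered therapy, CBT and other apps. Exclusion 6 in section 6.1.2 concerns therapy before entry only.

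Section 10.1 makes ITT primary and adds a second analysis: "As a sensitivity analysis, the primary outcome will be analysed using the Per-Protocol (PP) population, which consists of participants complying with the treatment regimen". The next sentence says what complying means: "Compliance will be defined as a minimum of 60 minutes of total use for the intervention group, and one or more sessions of CBT" for controls. The same two thresholds appear earlier in the section. Neither statement mentions the other arm's treatment.

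The month 1, 3, 6 and 12 lists in section 7.10 all include this item: "Any change in medication (particularly medications known to be associated with tinnitus, e.g. Aspirin, diuretics) or introduction of hearing aid". From month 3 they also cover tinnitus-related appointments and out-of-pocket costs. Appendix 3 allows this in the control therapist's management plan: "Relaxation Therapy: Exercises, apps, refer to physio where indicated/available".

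**The concern.** In a non-inferiority trial, anything that makes the arms more alike helps the claim. The trial is open-label. The Oto programme takes about six weeks and the primary TFI is at six months, so an Oto participant who is still troubled has time to look for a therapist. If therapist therapy is the better treatment, that participant's later score improves and the Oto arm looks closer to control than it should.

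ITT keeps such participants by design. The per-protocol analysis is the only other analysis population section 10.1 names for the primary outcome, and its definition removes a crossover only if that person also fell short of the minimum exposure. Agreement between the two results would look reassuring without having tested for this bias.

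**Working it through.** **Who stays per-protocol under section 10.1**

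- Oto participant, 60 minutes of use, then a course of outside therapist CBT: stays in.
- Control participant, one session, then Oto despite the section 8.2 agreement: stays in.
- Oto participant who stops before 60 minutes and then sees a therapist: removed, but for low exposure.

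**Inputs (section 10.2):** margin 13 points, SD 31, 90 per group, one-sided 2.5%.

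**The plan's own figure.** n per group = 2 × (31/13)² × (z_α + z_β)². At 90% power this is 2 × 5.686 × (1.960 + 1.282)² ≈ 120; at 80% power it is 2 × 5.686 × (1.960 + 0.842)² ≈ 90. The stated 90 therefore matches 80% power, not the stated 90%. That is a separate matter: the calculation below needs only the 90 per group and the SD.

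**Effect of Oto-arm crossover.** Let the true difference (Oto minus control, positive meaning Oto is worse) equal the margin, so that declaring non-inferiority is an error. Assume a share p of the Oto arm gains the full benefit of therapist therapy.

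- SE = 31 × √(2/90) = 4.62.
- Non-inferiority is declared when estimate + 1.96 × 4.62 < 13, that is, when the estimate is below 13 − 9.06 = 3.94.
- The mean of the estimate is 13 × (1 − p).
- P(false non-inferiority) = Φ((3.94 − 13(1 − p)) / 4.62).

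| p (assumed) | mean difference | z | false non-inferiority |
|---|---|---|---|
| 0 | 13.00 | −1.96 | 2.5% |
| 5% | 12.35 | −1.82 | 3.4% |
| 10% | 11.70 | −1.68 | 4.7% |

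Where crossovers met the 60-minute minimum, the per-protocol estimate is diluted in the same direction.

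**What excluding crossovers could do.** Suppose the 10% of the Oto arm most inclined to seek therapy are excluded, and that inclination (taken as normal) correlates r with a worse TFI. The mean of those left improves by 31 × r × φ(1.282)/0.90 = 31 × r × 0.195 ≈ 6.0 × r points. The dilution at p = 10% is 13 × 0.10 = 1.3 points. Above r ≈ 1.3/6.0 ≈ 0.22, the exclusion moves the result towards Oto by more than the dilution it removes. Exclusion alone is therefore not a sufficient remedy.

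**The case against.** Several points on the other side stand and limit the finding.

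- **Direction.** A reader might infer that crossover in either arm favours the claim. The protocol does not support that. Control treatment is at least one therapist session, so a control participant who also uses Oto is most likely adding to therapy. If Oto helps at all, the control arm improves and the comparison moves against non-inferiority. The calculation covers the Oto-arm route only.
- **Recording.** A reader might infer that outside treatment goes unseen. The section 7.10 lists are open-ended, and appointments and out-of-pocket costs would pick up part of it. What remains true is that no listed item asks about tinnitus apps or therapy outside the allocated arm, and none feeds the per-protocol set.
- **Appendix 3.** Apps are listed there under relaxation therapy, and a relaxation app need not be a tinnitus app. This is an ambiguity with section 8.2, not a flat contradiction.
- **Rate.** The same formula gives 8.1% at p = 20% and 13.2% at p = 30%, but nothing in the protocol supports such rates. Section 7.9 concerns referral for an audiogram and section 8.3 referral for hearing aids. The synopsis describes CBT access as limited, and section 8.2 mentions long waits after GP referral.
- **Left to the SAP.** Section 10 calls itself an overview, and compliance with the regimen could be read as excluding crossovers. But the protocol goes on to define compliance explicitly, and that definition omits them. A SAP also cannot analyse crossover that was never recorded.

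**Conclusion.** The point holds in a limited form. The restriction on outside treatment is stated for one arm only, and the per-protocol rule as written retains participants who met minimum exposure and also received the other arm's treatment. For Oto participants who obtain therapist therapy, ITT and per-protocol share a bias towards non-inferiority if Oto is truly worse. The inflation is modest at low crossover, from 2.5% to 3.4% at 5% and 4.7% at 10%. Those figures assume a true deficit exactly at the margin and full therapist benefit for each crossover; partial benefit would give less. Control-arm use of Oto breaches the section 8.2 agreement and also stays per-protocol, but would more likely count against the claim. The plan should be changed: the correction is cheap, and crossover that goes unrecorded is hard to reconstruct later.

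**What to change.** 1. **Per-protocol definition (section 10.1).** Add as an exclusion receipt of the other arm's treatment before the month-6 TFI: for controls, Oto or another tinnitus app; for the Oto arm, therapist-delivered tinnitus therapy or CBT outside the trial. Leave the ITT set unchanged.
2. **Companion sensitivity analysis.** Because those who seek outside therapy may be doing badly, keep all randomised participants, treat TFI after crossover as missing, and impute it with the multiple imputation already planned in section 10.4, using earlier TFI scores. This assumes that those earlier scores account for who crosses over. Read it alongside the per-protocol result.
3. **Data.** Add one dated yes/no item to the existing follow-up questionnaires in both arms, on use of any tinnitus app or tinnitus or psychological therapy outside the allocated arm. Report crossover by arm.
4. **Wording.** Reconcile sections 8.1, 8.2 and 8.3 and the mention of apps in Appendix 3 on what outside treatment each arm may use. Which rule to adopt is for the sponsor and the investigator.

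Cost: protocol and SAP wording, one extra question, a slightly smaller per-protocol set, and possible selection within that set, which item 2 is there to examine.

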## 7.1 Digital Applications

For the duration of the trial participants will be asked to record their responses to questionnaires directly into the Lindus Health Electronic Data Capture (EDC) platform, via a participant survey link, which will be emailed and/or texted to them. The participants in the smartphone delivered CBT arm will also use the Oto tinnitus app. Certain fields may require duplicate data entry between the two digital systems, but it is essential that data on the Lindus Health platform is completed fully.

The Lindus Health team will have access to the EDC data and will review this on a daily basis (excluding weekends). Missing data will trigger an alert message to the participant via text/email. If no response is entered, a daily reminder will be triggered for 3 days, after which point the Lindus Health team will contact the participant to assess if they wish to withdraw from the study. If a participant wishes to withdraw then they will be advised to arrange an appointment with their GP or healthcare provider to discuss other treatment options (i.e. return to standard care), and a reason for withdrawal will be documented. Free access to the app will continue for participants in the Oto arm, or be offered free for 12 months from completion of the study for participants in the control group.

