## 7.6 Randomisation

Following confirmation of eligibility, the participant will be randomised using a secure, fully validated and compliant web-based randomisation system called Sealed Envelope.

Participants will be randomised into one of the two groups at a ratio of 1:1, stratified by

1. Age (<40, >=41-<=60, >61)
2. Sex (Male, Female)
3. Pure tone average threshold based on home hearing test (mean threshold at 0.5, 1, 2, 4 kHz (‘None’ <=15dB, ‘Slight’ 16-25dB, ‘Mild’ 26-40dB, ‘Moderate’ 41-55dB, ‘Moderately severe’ 56-70dB, ‘Severe’ 71-90dB, ‘Profond‘ 91dB+)

1. Control arm: participants will receive one to one therapist-delivered tinnitus therapy from an audiologist/hearing therapist. The specification for the tinnitus therapy to be provided as a control intervention can be found in Appendix 3. This will be delivered remotely, and will consist of a minimum of 1 session, with further sessions at the discretion of the participant and therapist up to a maximum of 6. Therapy will begin within +/- 1 week of randomisation. There will be a panel of therapists selected to deliver the therapy, with all individuals having experience of NHS tinnitus care. The therapy provided will broadly conform to the standard NHS treatment as outlined below.
2. Intervention arm: participants will receive the Oto tinnitus programme (smartphone app delivered CBT). This includes an evaluation of symptoms and tinnitus severity, CBT, mindfulness and other interventions. More details on the Oto app can be found here: <https://www.joinoto.com>

A member of the central trial team will inform the participant during their eligibility call or directly call the participant to inform them of their randomisation allocation, and they will also be sent an email confirmation.

Randomisation represents trial day 1 and outcome assessments will be timed from this point.

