### 7.10.4 Month 12 (Study week 52 +/- 28 days)

To collect data to include but not limited to:

- Complete TFI questionnaire
- Complete EQ-5D-5L and HUI3 questionnaires
- Complete questionnaire on primary and community healthcare appointments and A&E visits related to tinnitus since week 26
- Complete questionnaire on personal out-of-pocket tinnitus related costs, any time-off work and travel information to appointments incurred since week 26
- Any change in medication (particularly medications known to be associated with tinnitus, e.g. Aspirin, diuretics) or introduction of hearing aid

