## 17.6 Expenses and Benefits

Participants in the smartphone app delivered arm will receive free access to the intervention for the 12 months of the study. Those in the control group will receive a free subscription to the Oto tinnitus programme at the end of the 12 month trial period.

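### The protocol gives control-arm access to Oto several release points that do not match, and one of them can fall before the month 12 forms are returned

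*Protocol*

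**What the plan says.** Four statements in the protocol bear on when a control participant may use Oto.

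- **Offer, Section 8.2:** "participants in the control group will be offered the Oto Tinnitus Programme at the end of the 12-month RCT period". The stated purpose is retention.
- **Offer, Section 17.6:** "Those in the control group will receive a free subscription to the Oto tinnitus programme at the end of the 12 month trial period".
- **Offer, Section 7.1:** free access is to "be offered free for 12 months from completion of the study for participants in the control group". This sits in a paragraph about participants who stop responding or withdraw.
- **Bar, Section 8.2:** "Participants in the control group will agree to not use Oto or an alternative tinnitus app for the duration of the study".

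The only definition of when the study finishes is in Section 7.12: "The end of the study is defined as the last participant’s last data capture".

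On the assessment side, Section 7.6 states: "Randomisation represents trial day 1 and outcome assessments will be timed from this point". The heading of Section 7.10.4 begins "Month 12 (Study week 52 +/- 28 days", and that visit collects TFI, EQ-5D-5L, HUI3, resource use and out-of-pocket costs. Section 10.4 treats a patient-reported outcome as missing only if it falls outside its window, so a form returned late but within the window counts. No section makes Oto access conditional on the participant's own month 12 form.

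**The concern.** Sections 8.2 and 17.6 tie the offer to a period of time, not to the last assessment. If access opens on the 12-month date, a control who replies late in the window may already be using the trial intervention. Only the control arm is exposed to this, and whether it happens depends on how late the participant replies.

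The outcomes at stake are the 12-month TFI total and subscales, the 12-month EQ-5D-5L and HUI3 utilities, and the closing point of the QALY curve in the one-year cost-utility analysis. Opening access before the final form would also weaken the retention incentive that Section 8.2 gives as its reason for the offer.

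Separately, the four statements cannot all be followed as written. If the study ends only as Section 7.12 defines it, a control randomised early is offered Oto at 12 months while still bound not to use it.

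**Working it through.** The protocol states no figure for this overlap, so there is none to reproduce. The check has three parts.

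**1. Release point under each reading**

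| Reading | Source | Access opens | Overlap with a valid month 12 form |
|---|---|---|---|
| Calendar | 8.2 (offer), 17.6 | 12 months after randomisation | possible, see part 2 |
| Participant's completion | 7.1, if completion means the individual's | after that participant's last form | 0 days |
| Whole study | 7.1 and the bar in 8.2, read with 7.12 | after everyone's last form | 0 days |

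The bar does not settle which reading applies. If the study means the whole trial, the bar contradicts the offer in the same section. The synopsis gives a study duration of 18 months. If that runs from the first randomisation (an assumption), the contradiction could last up to 18 − 12 = 6 months for the earliest controls. If the study means the individual's 12 months, the bar lapses when the offer is made and late forms are not protected.

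**2. Length of overlap under the calendar reading**

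Inputs: randomisation is day 1 (7.6); release is taken as day 365 (assumption); the window extends 28 days past week 52 (7.10.4); the programme lasts about 6 weeks, or 42 days (8.1).

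Overlap = (nominal visit day + 28) − 365. Share of programme = overlap / 42.

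| How week 52 is counted | Nominal day | Window closes | Overlap | Share of 42 days |
|---|---|---|---|---|
| First day of week 52 (as in Appendix 2) | 51 × 7 + 1 = 358 | 386 | 21 days | 50% |
| 52 completed weeks | 52 × 7 = 364 | 392 | 27 days | 64% |
| Day 365 | 365 | 393 | 28 days | 67% |

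These are maxima: they need uptake on the day of release and a reply on the last day of the window. Section 5.2 places a one-week onboarding before the 12 months. If that week follows randomisation, each overlap shortens by 7 days.

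**3. Possible effect, under assumed inputs**

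The protocol gives neither the share of controls who would reply after starting Oto (f) nor their gain. The ranges below are assumptions, used only to show scale.

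TFI: shift in control mean = f × gain, with gains of 5 to 13 points.

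- f = 10%: 0.5 to 1.3 points
- f = 25%: 1.25 to 3.25 points
- f = 50%: 2.5 to 6.5 points

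The top value is half of 13, the non-inferiority margin that Section 10.2 sets for the 6-month outcome.

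QALYs: raising only the final utility by u over a half-year segment, with linear interpolation (11.1), adds 0.5 × 0.5 × u × f to the control mean. With u = 0.02 and f = 10% this is 0.0005. With u = 0.05 and f = 50% it is 0.00625.

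A higher TFI is worse, so a gain lowers the control mean and favours control over Oto.

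**The case against.** The strongest reply is that the protocol, read as a whole, already prevents early crossover. Controls agree not to use Oto during the study, Section 7.1 starts access at completion, the flow chart in Appendix 1 puts the month 12 follow-up before the end of the trial, and an offer meant to aid retention makes most sense after the last form. No sentence names week 52 or day 365 as the release date. All of this stands, and it means that contamination is possible under one reading and is not built into the plan. It does not remove the inconsistency: the bar either conflicts with the offer or expires with it, and the wording in Section 7.1 sits in a passage about withdrawal.

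A reader might infer three stronger things that the documents do not support.

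- **That 12-month control data will be collected after crossover.** This follows only from the calendar reading.
- **That about half of control forms are exposed, because half of the window lies after week 52.** This needs replies spread evenly over the window. The protocol gives no such distribution, and the alerts, daily reminders and staff contact in Sections 7.1 and 10.4 should shorten delays.
- **That crossover would pull the arms together.** This needs controls to be worse than the Oto arm at 12 months. Section 11.1 expects similar QALYs. If the arms are similar, added benefit in controls would separate them in favour of control.

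How to analyse any form completed after access can properly be left to the SAP.

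**Conclusion.** The point holds as an inconsistency with a limited consequence. The protocol's release points for control access to Oto do not agree, and it never defines for an individual when the 12-month period ends. Under the calendar reading, a valid month 12 form can follow up to 21 to 28 days of possible Oto access, which is 50% to 67% of the programme. Under the other readings the overlap is 0 days. The range rests on release at day 365 counted from randomisation and on how week 52 is counted.

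The share of controls affected is unknown, so the TFI and QALY shifts above are illustrations and not estimates. The probable direction is to flatter control. The reach is the 12-month TFI, utilities, resource use and last QALY segment. The 6-month primary outcome, and the superiority objective at the same time point, are unaffected. The matter is still worth settling in the protocol, because later analysis cannot fully undo crossover that precedes the assessment.

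**What to change.** Reconcile Sections 7.1, 8.2 and 17.6 to one participant-level trigger: control access to Oto opens only once that participant's month 12 questionnaires have been received, or the month 12 window has closed. Word the no-Oto agreement in Section 8.2 to end at the same point, so that it no longer depends on the whole-trial definition in Section 7.12. Record the date on which access opens for each control, so that its order relative to the month 12 form can be verified.

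This brings the overlap to 0 days. The cost is a wording amendment and one recorded date. Some controls, namely those who reply late or not at all, would wait up to about 4 weeks longer for free access than under a calendar release.
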